### Sample Size

A total of 360 patients will be enrolled across 3 participating centers: Hospital Universitario de Santiago de Compostela, Spain (120/360, 33.3%); Clinic Königsfeld of the German Pension Fund at the University of Witten/Herdecke, Ennepetal, Germany (120/360, 33.3%); and Elisabeth-TweeSteden Hospital, Tilburg, the Netherlands (120/360, 33.3%). At each center, patients will be randomly assigned, with 60 (50%) out of 120 receiving the intervention in addition to care as usual, and 60 (50%) receiving care as usual. Of 360 patients, 180 (50%) will receive the intervention, and 180 (50%) patients will receive care as usual.

On the basis of participation rates in previous randomized controlled trials [33], it is expected that approximately 33% of patients will decline participation. It is expected that a total of 480 patients will have to be approached to include 360 participants across the 3 study sites. Sample size calculations were based on medium-large effect sizes and statistical power analyses were conducted using G*Power (version 3.1.9.4; Heinrich-Heine-Universität Düsseldorf) [34]. A sample of 120 patients per center will enable detection of a medium effect size. The *f*^2^ for the between-within group interaction is 0.15 in a mixed model ANOVA, with a power of 0.80 and a two-sided α level of 0.025 (0.05/2, as two primary outcomes will be evaluated; details are provided in the *Study Objective* section). In brief, the set of variables for this analysis was based on a 2 (between-group: intervention vs control)×2 (repeated measures at baseline and 6 months) mixed model ANOVA, assuming sphericity and a correlation of 0.3 between the repeated measures.

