### Randomization and Blinding

Participants will be randomly assigned (1:1) to either the intervention group or the care-as-usual group. A computer-generated randomization sequence will be delivered, in an Excel (Microsoft Corp) file, to each recruitment site and will be concealed by one of the researchers by covering the allocation numbers with “black paint.” Randomization will be conducted and dated, per patient, by the researcher after the participant has signed the informed consent and baseline assessments have been performed.

Given the nature of the study, blinding of the researchers or participants during the behavioral intervention trial is not possible. However, the analysis of blood samples and all other outcome measures will be conducted by research team members who are blinded to the participants’ group assignment.

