### Statistical Analysis

For descriptive statistics, categorical variables will be compared with the *χ*^2^ test (Fisher exact test when appropriate). Continuous variables will be compared using independent sample *t* test or a nonparametric test where appropriate.

To address the main hypothesis, repeated measures ANOVA using generalized linear mixed modeling analysis will be used to investigate the effect of the intervention on changes from baseline to 6 months for the 2 primary end points (Coropredict score and a 6-minute walk test) using a 2 (intervention vs control)×2 (baseline to 6 months) design, accounting for potential baseline differences and correlations between baseline and 6 months assessments. Data for the primary outcomes will be analyzed according to the intention-to-treat principle.

For the secondary outcome measures, a similar approach will be used. To explore long-term effects at 12 months, 2 (group)×3 (repeated measure) mixed models will be used. In addition, univariable and multivariable regression analyses (both linear and logistic regression) will be used to examine cross-sectional and longitudinal associations between variables, with the type of regression analysis depending on the distribution characteristics of the variables.

Exploratory analyses will also include completer analyses and evaluation of trial adherence as related to the outcome measures. As this study includes multiple secondary outcome measures without correction for statistical type 1 error, the obtained results will be interpreted with caution and will primarily provide estimates of effect sizes related to the TIMELY intervention. Data will be analyzed using SPSS statistics (IBM Corp) [48] or equivalent.

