### Limitations

Given the involvement of 3 different recruitment centers with varying phase-2 CR procedures (inpatient vs outpatient CR), patient enrollment procedures might be slightly different between centers. While these differences are not expected to affect the results of the study, it is important to note that patients may be approached at different time points during or following their center-based CR. Furthermore, participants will receive several monitoring devices and extensive instructions on navigating the TIMELY app. This could be perceived by some patients as overwhelming and perhaps result in refusal or early termination of participation. Finally, as the TIMELY intervention will provide personalized advice based on incoming patient data, the intervention may be more effective for those providing data frequently.

The results of the TIMELY intervention will provide insights into the effectiveness of a fully web-based, personalized program to support long-term cardiac healthy behavior and reduce cardiac risk. The results will also provide further understanding of relevant factors contributing to successful health behavior change over time and those that help sustain these behaviors. In addition, the TIMELY project can provide new insights into which BCTs are associated with successful behavior change, helping to enhance the effectiveness of future interventions.

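### Allocation is fixed within each of three centers, but the described primary model does not name center; if centers differ in 6-month change (or in level, with baseline as a covariate), the reported standard error will be too large

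*Protocol article*

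**What the plan says.** **Allocation.** The Sample Size section states: "At each center, patients will be randomly assigned, with 60 (50%) out of 120 receiving the intervention in addition to care as usual". The other 60 receive care as usual, and the same split applies at all three centers, for 360 in total. Randomization and Blinding gives a 1:1 ratio and says that the computer-generated sequence is delivered "to each recruitment site and will be concealed by one of the researchers". The article does not use the word stratified, but a 60:60 split planned at each center from a list held at each site makes center a balancing factor.

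**Analysis.** Statistical Analysis describes a mixed model for both primary outcomes (CoroPredict score and 6-minute walk distance) as a 2 (group) x 2 (baseline, 6 months) "design, accounting for potential baseline differences and correlations between baseline and 6 months assessments". Secondary outcomes follow a similar approach, and the 12-month analysis is a 2 x 3 version. Center is named in none of these, nor in the power set-up.

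**Center differences.** The Limitations section reports that phase-2 rehabilitation is inpatient at some centers and outpatient at others, and that patients may be approached at different times relative to it. The authors add that they do not expect these differences to alter the findings. No between-center variance is given anywhere.

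**The concern.** When allocation is balanced on a factor, differences between levels of that factor cannot contribute to the difference between arms. A model that omits the factor still counts those differences as residual noise, so it reports a standard error larger than the real sampling variability. Intervals are then wider than the design warrants and tests reject less often than their nominal level.

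The article gives some reason to think that centers could differ in change as well as in level. Baseline may fall at different stages of recovery, because patients are approached at different times. Usual care is unrestricted, and the Introduction describes phase-3 support as uneven and dependent on reimbursement. What is at stake is precision, for the two primary outcomes and also for the secondary outcomes, which the article says will mainly be read as effect-size estimates.

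**Working it through.** **1. The plan's own figure.** The design assumes a value of 0.15 (labelled f²) for the group-by-time interaction, "with a power of 0.80 and a two-sided α level of 0.025", and a correlation of 0.3 between the two measurements. The noncentral F calculation uses λ = N·m·f²/(1 − ρ), with m = 2 and 1 and N − 2 degrees of freedom.

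- f = 0.15, α = 0.025: power at N = 120 is 0.694, and 152 patients are needed for 0.80.
- f² = 0.15 (f = 0.387), α = 0.025: 26 patients are needed.
- f = 0.15, α = 0.05: power at N = 120 is 0.787, and 126 patients are needed.
- f = 0.15, α = 0.025, N = 360: λ = 360 × 2 × 0.0225/0.7 = 23.1, power 0.995.

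The stated 120 per center is not reproduced under the stated inputs. That is a separate matter and does not affect this point. The last line gives the margin at the full trial size.

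**2. Which center differences matter.** With complete data, the group-by-time effect in a 2 x 2 design is the difference between arms in mean change. A center shift present at both visits subtracts out within each patient. A center shift in change does not. If baseline is instead a covariate, part of a level shift also remains in the residual.

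This was checked by simulation: three centers, 60:60 in each, correlation 0.3, outcome SD 1 within center, 4,000 runs. Entries are mean reported standard errors.

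| Center differences assumed | Analysis | Without center | With center |
|---|---|---|---|
| None | change | 0.1245 | 0.1245 |
| Level only, 20% of variance | change | 0.1246 | 0.1246 |
| Change, 5% of change variance | change | 0.1278 | 0.1246 |
| Level 20% plus change 10% | change | 0.1315 | 0.1246 |
| Level only, 20% | baseline as covariate | 0.1059 | 0.1006 |
| Level 20% plus change 5% | baseline as covariate | 0.1166 | 0.1006 |

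In the change analyses with a center difference in change, the actual SD of the estimate was 0.123 to 0.125 whether or not center was in the model. The excess is therefore in the reported standard error, not in the estimate.

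**3. Size.** Let c be the share of the variance of the analysed quantity that center explains. That quantity is the change score in the repeated-measures form, or the baseline-adjusted outcome. The documents give no value for c, so a range is assumed.

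- Ratio of standard errors, without to with center: 1/√(1 − c).
- Extra patients needed to bring the reported standard error back: 360/(1 − c) − 360.
- Actual two-sided error rate at nominal 0.025: 2[1 − Φ(2.241/√(1 − c))].
- Power without center, for an effect that has 80% power with center in the model: Φ(3.083 − 2.241/√(1 − c)), where 3.083 = 2.241 + 0.842. This takes the true variability as unchanged, as the simulation showed for the change analysis.

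| c | SE too large by | Extra patients | Actual type I error | Power |
|---|---|---|---|---|
| 0.05 | 2.6% | 19 | 0.0215 | 78.3% |
| 0.10 | 5.4% | 40 | 0.0181 | 76.4% |
| 0.15 | 8.5% | 64 | 0.0151 | 74.3% |

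At the design effect read as f = 0.15 with N = 360, √λ = 4.81. With c = 0.15 omitted, power is Φ(4.81 − 2.241/√0.85) = Φ(2.38) = 0.991, against 0.995.

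**The case against.** The strongest reply is that the article is condensed. It gives the factorial form and two things the model accounts for, and it never says that center is excluded. Covariates are often left to a full protocol or analysis plan, and neither is shown. That stands as a limit on the claim: a reader might infer that the trial will be analysed without center, but the text supports only that center is not named. The point remains worth raising because the article does state what the model accounts for, and the factor used for allocation is not among those items.

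Second, a reader might infer that leaving out center enlarges the standard error as a matter of course. It does not. The tested effect is group by time, and constant level differences cancel; in the simulation, a 20% level difference left the standard error at 0.1246 either way. The documents do not establish that centers differ in 6-month change, and the authors say they expect no effect on results. That expectation comes without data. It leaves the size unknown and is not a reason to omit a balancing factor.

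Third, the harm is small and in the safe direction. This also stands: at f = 0.15 and 360 patients, power stays above 0.99 over the range shown.

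**Conclusion.** The point holds in conditional form. The described model does not name the factor within which allocation was fixed. If centers differ in change to 6 months, or differ in level when baseline is a covariate, the reported standard error is too large: by 2.6%, 5.4% or 8.5% for assumed shares of 5%, 10% or 15%. These must be shares of the variance of the change score or of the baseline-adjusted outcome; a share of raw outcome variance could be pure level difference, which costs nothing in the repeated-measures form.

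It would be wrong to read this as a threat to validity. The treatment estimate is not biased and the error rate falls below nominal, so a significant result would not be undermined. The possible loss is in interval width and in power for effects smaller than the design effect. The figures assume the planned 60:60 split in each center, complete data, and a continuous outcome analysed on its own scale. The article reports 180 and 178 randomized overall and no split by center.

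**What to change.** State that every efficacy model includes center as a fixed effect (two indicators). In a baseline-adjusted model of the 6-month value, the center main effect is enough. In the 2 x 2 and 2 x 3 repeated-measures forms, add center-by-time as well, because a center main effect alone leaves the group-by-time contrast unchanged. Say which of the two forms accounting for baseline differences refers to. Report the treatment effect by center descriptively, without a test. If an analysis plan already specifies center, align the published description with it.

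The choice should be recorded and dated before results are seen. The article reports 6-month follow-up complete by January 2025 and results expected in September 2025, so a later addition could look data-driven.

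The cost is wording and two degrees of freedom (four with center-by-time at two visits) out of about 358. Center is known for every patient, so no new data are needed.

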## Results

A total of 809 patients were approached for participation. A subgroup (n=451) was excluded for not meeting the inclusion criteria or declined participation for various reasons (eg, travel burden to the hospital or perceiving the intervention as too demanding). Finally, a total of 358 patients were randomly assigned to either the intervention (n=180, 50.1%) or the care-as-usual (n=178, 49.7%) condition. In Figure 4, a schematic representation of the trial is provided, indicating the different stages of assessments. As of January 2025, all patients have completed the 6-month follow-up. The 12-month follow-up is currently underway and is expected to be completed by May 2025. Following data cleaning and analysis, results are anticipated by September 2025.

**Figure 4 figure4:**
[figure not shown]
A schematic representation of the TIMELY trial.

## Discussion

### Anticipated Findings

Lifestyle behaviors are a recognized risk factor and account for a significant proportion of the disease burden among people with CAD [2,21-23]. Eliminating or attenuating of these behaviors is warranted, as up to 80% of cardiovascular events can be prevented by adopting a healthy lifestyle [49,50]. However, changing and maintaining healthy behaviors is challenging, and only a subgroup of people tends to adhere to the guideline recommendations and succeed in long-term behavior change [51]. CR programs (provided online or face-to-face) are successful in changing health behaviors; however, maintaining the gains accomplished during the initial phases of CR remains challenging and requires additional support [26]. To maintain the benefits of CR, eHealth has been identified as a potentially effective approach. However, there are still gaps in the evidence supporting its use [52]. This mode of delivery provides personalized yet scalable care to those who need it. Hence, the TIMELY project aims to evaluate the effectiveness of the described patient-centered eHealth-based maintenance program, composed of an integrative care platform and an app-based, long-term health behavior change program. It is expected that supporting patients with CAD using technological innovations and applying patient-tailored and behavior-specific change techniques or domain-specific BCTs may result in significant and relevant improvements compared to care as usual. The TIMELY project goes beyond the current state-of-the-art by (1) using a highly personalized approach supported by AI technology; (2) providing a fully eHealth supported program; (3) including effective BCTs per target behavior; (4) focusing on both mental and physical factors; and (5) including the perspectives of all relevant stakeholders. In addition, evaluating cost-effectiveness is crucial for determining the economic value of the TIMELY project’s eHealth-based maintenance program. Integrating a cost-effectiveness analysis will measure not only the costs associated with implementing and using the integrative care platform and the app but also the economic benefits derived from improved health and reduced future events. This analysis will help justify the investment in these technologies by demonstrating that the proposed solutions are not only effective in terms of health outcomes but also economically efficient.

### Limitations

Given the involvement of 3 different recruitment centers with varying phase-2 CR procedures (inpatient vs outpatient CR), patient enrollment procedures might be slightly different between centers. While these differences are not expected to affect the results of the study, it is important to note that patients may be approached at different time points during or following their center-based CR. Furthermore, participants will receive several monitoring devices and extensive instructions on navigating the TIMELY app. This could be perceived by some patients as overwhelming and perhaps result in refusal or early termination of participation. Finally, as the TIMELY intervention will provide personalized advice based on incoming patient data, the intervention may be more effective for those providing data frequently.

The results of the TIMELY intervention will provide insights into the effectiveness of a fully web-based, personalized program to support long-term cardiac healthy behavior and reduce cardiac risk. The results will also provide further understanding of relevant factors contributing to successful health behavior change over time and those that help sustain these behaviors. In addition, the TIMELY project can provide new insights into which BCTs are associated with successful behavior change, helping to enhance the effectiveness of future interventions.

## Appendix

Multimedia Appendix 1 Biological specimens.

## Abbreviations

AI: artificial intelligence
BCT: behavior change technique
BP: blood pressure
CAD: coronary artery disease
CR: cardiac rehabilitation
DSS: decision support system
ECG: electrocardiogram
EP: exercise prescription
PROM: patient-reported outcome measure
